### Safety Analysis

An adverse event is a new occurrence of a symptom after study medication administration that was not observed before administration and includes unintended consequences such as abnormal laboratory findings, symptoms, and temporary events related to the study medications. The severity of adverse events, both self-reported and non–self-reported, will be assessed by the investigator by applying Spilker’s classification as follows: mild, not requiring additional intervention, nor significantly inhibiting the normal lifestyle (function) of the participant; moderate, significantly inhibiting the normal lifestyle (function) of the participant and may need additional intervention, recovering afterward; severe, severe adverse events requiring intensive intervention; and leaving sequelae. The causal relationship between adverse events and the study medication will be assessed by the investigator using the following six-level grading scale: (1) definitely related, (2) possibly related, (3) probably related, (4) not related, (5) definitely not related, and (6) unknown.

For all adverse events and abnormal findings on examination, the symptoms, frequency, and degree of relationship with the study medication were recorded in detail for each group. The number and proportion of participants in whom adverse events occurred at least once, 95% CI, and number of occurrences within each group will be presented. Differences in proportions between groups will be tested using the chi-square test or Fisher exact test.

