**Exclusion criteria**
Diagnosis of degenerative brain diseases (eg, Parkinson’s disease, Alzheimer disease, etc).Have a brain condition other than ischemic stroke (eg, brain tumor, traumatic brain injury, arteriovenous malformation, Moyamoya disease, and stroke due to these conditions).Unstable vital signs at screening (eg, systolic blood pressure greater than 160 mm Hg despite taking blood pressure medications).Serious medical condition (eg, liver cirrhosis, chronic kidney disease stage V, or severe heart failure of New York Heart Association (NYHA) grade III or greater).History of malignancy, including leukemia and lymphoma, within the past 5 years.Hepatic and renal dysfunctions.Aspartate aminotransferase, alanine aminotransferase ≥2 times the upper limit of normal at screening.An estimated glomerular filtration rate < 60 mL/min/1.73 m2 at screening.Within 24 hours of onset.Patients with Korean National Institutes of Health Stroke Scale (K-NIHSS) score 21 to 42.Pregnant, nurses, or women of childbearing potential who have negative pregnancy test results and have not agreed to use contraception during the study.Previously experienced hypersensitivity after taking HH333’s constituent medicines *Scutellariae radix*, *Coptidis rhizoma*, *Phellodendri cortex*, *Gardeniae fructus*, and *Rhei rhizoma*.Any other study medications administered within 30 days prior to screening.Patients who have not been administered the study medication or who have participated in a simple observational clinical trial are eligible.Difficulty taking the doses required in this study.Judged by the investigator as nonconformity for participation in the trial for any reason.Plans to use anticoagulants during the study or have difficulty discontinuing them.

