### Safety Assessments and Monitoring

At each visit, participants will be screened for adverse events, laboratory tests, urine findings, electrocardiograms, hemorrhagic events such as cerebral hemorrhage or gastrointestinal bleeding related to antiplatelet or anticoagulant use, vital signs, and physical examinations. Laboratory findings included complete blood count (red blood cells, hemoglobin, hematocrit, platelets, and white blood cells) and biochemistry (fasting blood sugar, blood urea nitrogen, creatinine, natrium, potassium, chloride, aspartate aminotransferase, alanine aminotransferase, C-reactive protein, calcium, and uric acid). Urine findings included specific gravity, pH, albumin or protein, glucose, ketone, bilirubin, occult blood, urobilinogen, nitrite, leukocytes, and human chorionic gonadotropin in women of childbearing age. Adverse events included both self-reported symptoms and those judged by the investigator and were collected until 30 days after the end of administration.

After collecting all adverse events that appeared as test findings and symptoms in each group, we compared the frequency and severity of adverse events between the groups and their relationship with the study medications. Adverse events that are not related to the study medications do not meet the criteria for dropout but allow the patient to receive the best possible care regardless of the study. If SAEs occur, the study will be stopped immediately, in part or in whole, and the study researcher will report it to the principal investigator and the institutional review board for appropriate action.

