Most patients with stroke have a multimorbidity status due to various risk factors such as high blood pressure, diabetes, and hyperlipidemia, and controlling risk factors is crucial, making them susceptible to polypharmacy [48]. In a study of the Scottish general population, patients with stroke were more than twice as likely to have multimorbidity compared to patients without stroke, with 12.6% of patients with stroke taking 11 or more medications compared to only 1.5% of patients without stroke [49]. Patients with stroke taking more than 5 or 6 medications are at increased risk for adverse events and falls [50,51], which can severely impact rehabilitation outcomes [48]. Since HH333 has effects on improving stroke risk factors [17], it is expected to complement or replace stroke risk factor therapies, thereby reducing medication use.

Although most herbal medicines are safe and rarely cause liver and kidney injury, some herbal medicines occasionally cause liver injury, and *Scutellariae radix*, a component herbal medicine of HH333, is the main causal herbal medicine responsible for herb-induced liver injury with about 1% of incidence [52]. However, there have been no studies on the dose-dependent toxicity of *Scutellariae radix*, but previous *in vivo* studies have reported no toxicity at a dose of 2000 mg/kg [53,54], which is a much higher dose than the *Scutellariae radix* dose of HH333. In addition, in a 656-patient safety study, no liver or kidney injury was reported with HH333, and mild adverse events of gastrointestinal symptoms, headache, insomnia, chest discomfort, fatigue, and thirst occurred in 2% of patients, with no SAEs [25]. No adverse events were reported in 771 patients in a retrospective cohort study of HH333 published to date [18-20,55]. Therefore, HH333 is expected to be safe with no adverse events, including liver or kidney injury.

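### The adverse event definition leaves out worsening of pre-existing symptoms or conditions, and is unclear for laboratory values already abnormal at baseline

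*Protocol article*

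**What the plan says.** The definition is one sentence in Safety Analysis. It begins: "An adverse event is a new occurrence of a symptom after study medication administration that was not observed before administration". It goes on to say that an adverse event "includes unintended consequences such as abnormal laboratory findings, symptoms, and temporary events related to the study medications".

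Safety Assessments and Monitoring describes collection. Events come from tests as well as complaints ("After collecting all adverse events that appeared as test findings and symptoms in each group"), and "Adverse events included both self-reported symptoms and those judged by the investigator".

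Safety Analysis then separates recording from analysis. On recording: "For all adverse events and abnormal findings on examination, the symptoms, frequency, and degree of relationship with the study medication were recorded". On analysis: "The number and proportion of participants in whom adverse events occurred at least once, 95% CI, and number of occurrences" are presented by group, and the proportions are compared by a chi-square or Fisher test.

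Two other places bear on the point. The liver enzyme exclusion is "Aspartate aminotransferase, alanine aminotransferase ≥2 times the upper limit of normal at screening", so a mildly raised value does not bar entry. The Discussion says that one constituent herb "is the main causal herbal medicine responsible for herb-induced liver injury with about 1% of incidence".

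**The concern.** The usual purpose of an adverse event definition is to capture any unfavourable change after the first dose, whether it starts from nothing or from an existing problem. This one is built on novelty. A participant who enters with dyspepsia, insomnia, fatigue or hypertension and deteriorates has a problem that was already there before dosing, so the first half of the sentence does not reach it.

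The trial is exposed to this. The Discussion describes most stroke patients as multimorbid, follow-up runs to day 750, and the earlier 656-patient safety study of HH333 reported complaints that are common at baseline after a stroke. Fatigue is even measured at day 0 as a secondary endpoint.

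Safety is a stated objective, and the Discussion already expects HH333 to be free of adverse events. A definition that omits worsening leans towards that expectation.

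**Working it through.** No figure in the article turns on the adverse event definition, so the check is mainly a reading of the text, followed by one bounded illustration.

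**1. Worsening of a pre-existing symptom or condition.**
- The first half of the definition requires the symptom to be new and absent before dosing. Worsening fails both conditions.
- The second half adds laboratory findings, symptoms and temporary events, but does not mention a change in severity or frequency.
- Safety Assessments and Monitoring, and the Table 1 footnote on adverse events, say who may report or judge an event. Neither states a comparison with baseline.
- Result: no passage includes worsening, and the stated rule excludes it.

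**2. Laboratory values.**
- Abnormal laboratory findings are named in the definition, and test findings are a source of events. AST and ALT are among the safety assessments scheduled at visits 2 to 10 in Table 1.
- Enzymes between 1 and 2 times the upper limit are allowed at entry. For such a participant, a later and larger value is an abnormal finding, but the abnormality itself is not new. The text does not say which of these facts decides.
- Recording covers adverse events and abnormal findings as two items, while the proportion compared between groups is specified for adverse events only. A rise filed only as an abnormal finding need not enter that comparison.
- Result: ambiguous, not excluded.

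**3. Relatedness.**
- The closing words of the definition, on relation to the study medications, can be read as limiting the laboratory part to related findings.
- The causality scale in the same section includes two unrelated grades, and Safety Assessments and Monitoring discusses unrelated adverse events.
- Result: elsewhere the article treats unrelated events as adverse events, so the definition's wording is in tension with it.

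**4. Size (illustration only).**
Let N be the participants per arm, r the true proportion with at least one adverse event, and q the share of those participants whose only events are worsening of something already present. Participants counted = N × r × (1 − q).
- N = 118 comes from Sample Size, and it reproduces from the 106 stated there: 106 / (1 − 0.10) = 117.8, rounded up to 118.
- r = 2% is the rate in the earlier HH333 safety study; r = 10% is assumed.
- q is not given anywhere; 10% to 50% is assumed.

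| r | True number, 118 × r | Counted, q = 10% | Counted, q = 50% |
|---|---|---|---|
| 2% | 2.36 | 2.12 | 1.18 |
| 10% | 11.8 | 10.62 | 5.9 |

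If q were equal in both arms, the difference in proportions would shrink by the factor (1 − q): r₁(1 − q) − r₀(1 − q) = (1 − q)(r₁ − r₀). If HH333 aggravates existing complaints more than placebo does, q is larger in that arm and the difference shrinks further.

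**The case against.** The strongest reply is that the sentence does not stop at new symptoms. It names abnormal laboratory findings, collection covers test results, and the investigator may judge an event to be present. A reader might infer that only symptoms count, or that a further rise of an already raised liver enzyme is not an adverse event. The text does not support either inference. A much higher value can be recorded as an abnormal laboratory finding, and it was not itself seen before dosing. This part of the objection stands.

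A reader might also try to size the problem from the 1% liver-injury figure: 118 × 0.01 = 1.18 expected cases, 0.99^118 = 0.305 chance of seeing none, and an upper one-sided 95% bound of 1 − 0.05^(1/118) = 2.5% if none are seen. The arithmetic is right, but the numbers follow from 118 participants and a 1% rate under any definition. They do not measure what this definition loses. The 1% also belongs to one herb, and the same paragraph reports no liver or kidney injury in 656 patients taking HH333. New liver injury from a normal baseline is captured even on the narrow reading.

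Some worsening is visible elsewhere: vital signs are safety assessments, and fatigue, depression and neurological scores are followed from baseline. That is true, but none of it puts the event into the adverse event proportion.

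Finally, a journal article condenses the full protocol, and case report form instructions or laboratory grading rules may exist there. That is a fair reason not to criticise missing detail. It does not excuse the definition, which the article states outright and which, as stated, excludes worsening.

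**Conclusion.** The point holds for symptoms and conditions present before dosing: the stated rule excludes their worsening, and with it their contribution to the between-group comparison of participants with at least one adverse event. For laboratory values the finding is weaker. They are included, but the rule is unclear when the baseline value is already abnormal, and the relatedness wording sits badly with the causality scale.

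Under-counting is a risk, not a demonstrated result. Its size would need the share of participants whose only events are worsening, which the document does not give; the table above rests on assumed shares. Loss of a liver signal is not shown. The conclusion assumes that sites apply the definition as written. Sites that already record worsening by habit would lose less, but practice could then differ across the three hospitals. The change is worth making, because safety is an objective of the trial and the correction is small.

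**What to change.** Replace the definition in Safety Analysis with wording to this effect: an adverse event is any untoward sign, symptom, disease or laboratory abnormality that newly occurs, or worsens in severity or frequency from baseline, after the first dose of study medication, regardless of relatedness. Add that laboratory changes are judged against the baseline value, which Table 1 already collects at screening.

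The reference to relatedness then leaves the definition and stays with the six-level causality scale, which removes the tension described above.

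The cost is one sentence and a matching case report form instruction. Adverse event counts will be slightly higher in both arms. By November 13, 2024, 12 of the planned 236 participants had been randomized and no data had been analysed, so on that date few records predated such a change. Records of participants enrolled before it would need a check for worsening, so that one definition applies throughout.

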### Randomization, Blinding, and Allocation Concealment

A total of 236 participants who met the criteria were assigned to the HH333 or control group at a ratio of 1:1 by a statistician independent of this clinical study, using the block randomization method with R 4.4.0 (Comprehensive R Archive Network). Patients and investigators will be blinded to prevent access to the allocation results. Patients will be blinded to the study medication they are administered because they are taking either the treatment medication or a placebo. The treatment medication and placebo will be identical in size, shape, and appearance and packaged in the same type of packaging.

For allocation concealment, an independent statistician who generates the random numbers delivers a randomization code to each clinical trial site in a sealed, impermeable envelope. The investigators at each site will open the randomization envelopes in sequence in front of the patients to assign participants, and the open envelopes will be kept separate.

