### Sample Size

In previous studies, ischemic stroke recurrence rates of 12.5%-12.8% over 24 months with conventional antiplatelet therapy (aspirin or dipyridamole) [22] and 1.7% over the same period with HH333 [19] were reported. Therefore, the sample size was 106 patients per group and 212 patients in total at 2 years with a control group (P_2_=0.125-0.128), HH333 group (P_1_=0.017), a significance level (α) of 5% and a target power of 80%. Finally, a dropout rate of 10% was considered, resulting in a sample size of 118 patients per group for a total of 236 patients.

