### Statistical Analysis

All statistical analyses were two-sided with a 5% significance level. The statistical program SAS (version 9.4 or more, SAS Institute) was used for the analysis. If at any point there are missing values or participants are dropped before the end of the study, the data will be treated as missing data. All data obtained from the participants were analyzed in 3 forms: full analysis set, per-protocol set, and safety set. Efficacy analysis will be conducted using the results of the full analysis set as the main analysis, and a per-protocol set analysis will be conducted separately to evaluate whether there are differences from the full analysis set results. Safety analysis was performed on the safety set and the safety of the study medications was evaluated. The full analysis set includes all data from participants with at least one efficacy assessment at the primary outcome after taking the study medication. The per-protocol set included participants who were eligible for full analysis and successfully completed the study. The safety set included all data from participants who received at least one dose of the study medication.

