Based on this evidence, the Korean Medicine Clinical Practice Guideline for Stroke, compiled by the Korean Ministry of Health and Welfare, recommends that HHT, the main component of HH333, may be considered for the treatment of ischemic stroke to improve neurological disability and prevent recurrence [56]. However, the recommendation is graded as C/Low because clinical studies of HH333 have only been conducted on hypertension and hyperlipidemia, which are risk factors for ischemic stroke, and experimental studies, literature reviews, or retrospective cohort studies on ischemic stroke, which are not sufficient for high quality. In modern clinical research, RCTs represent the highest level of evidence in evidence-based medicine, and significant results from RCTs are more conclusive than other types of clinical research information [57]. Therefore, in order to realize the possibility of HH333 as a therapeutic and recurrent prevention agent for ischemic stroke by improving the quality of evidence, we present a double-blind RCT compared with a placebo to evaluate the clinical effectiveness and safety of HH333 for ischemic stroke in patients with ischemia induced by small-vessel disease.

A limitation of this protocol is that it excluded patients at high risk of bleeding, such as those taking anticoagulants. This exclusion was made because it was important to exclude any factors that could influence bleeding propensity in this study, but it may limit the generalizability of the results.

We hypothesized that HH333 would be effective and safe in preventing recurrent ischemic stroke and improving neurological symptoms in patients with small-vessel disease induced by ischemic stroke. This clinical study will generate data on the therapeutic efficacy and safety of HH333 in ischemic stroke. If the results of this study prove the efficacy and safety of HH333, they will serve as a basis for further use of HH333 with ischemic stroke and will also contribute to the development of novel alternatives for the treatment and prevention of ischemic stroke.

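### The only between-group safety inference is a significance test of adverse event proportions; at 118 per group a non-significant result cannot support a conclusion that HH333 is safe

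*Protocol article*

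**What the plan says.** The Safety Analysis section plans, for each arm, the number and proportion of participants with at least one adverse event, with "95% CI, and number of occurrences within each group will be presented". It then fixes the comparison between arms: "Differences in proportions between groups will be tested using the chi-square test or Fisher exact test". The Statistical Analysis section sets the level: "All statistical analyses were two-sided with a 5% significance level". The Safety Assessments and Monitoring section adds a comparison without a named method: "we compared the frequency and severity of adverse events between the groups and their relationship with the study medications".

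The sample size rests on stroke recurrence alone, "resulting in a sample size of 118 patients per group for a total of 236 patients", with 1:1 allocation. The Discussion says that one component herb "is the main causal herbal medicine responsible for herb-induced liver injury with about 1% of incidence", expects HH333 to be free of adverse events, hypothesises that it is effective and safe, and continues: "If the results of this study prove the efficacy and safety of HH333, they will serve as a basis for further use".

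**The concern.** A superiority-type test can show that the arms differ. It cannot show that they are alike. If HH333 really adds harm, the test supports safety only by failing to reach significance, and in a trial of this size rare harms nearly always give that result.

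The within-arm interval does not fill the gap. It describes how often events occur on HH333 or on placebo, not how many more occur on HH333. As written, the article gives no interval for the difference between arms, which is the quantity a safety claim against placebo needs.

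At stake is the safety half of the conclusion. After 720 days of dosing, a null test could be cited for wider use although an excess of the size the article itself mentions had not been excluded.

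**Working it through.** **1. The plan's own figure (Sample Size section).** Inputs: 1.7% on HH333, 12.5% on control, two-sided 5%, 80% power. Mean rate 0.071, difference 0.108.

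- Uncorrected: n = [1.96·√(2·0.071·0.929) + 0.842·√(0.017·0.983 + 0.125·0.875)]² / 0.108² = 87.6, so 88.
- With continuity correction: (87.6/4)·[1 + √(1 + 4/(87.6·0.108))]² = 105.3, so 106, as stated.
- With 10% dropout: 106/0.9 = 117.8, so 118, as stated.

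Safety does not enter this calculation. The safety set is everyone with at least one dose, so up to 118 per group.

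**2. Events needed for significance when placebo has none (118 per group).**

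- Fisher: 5 vs 0 gives p = 0.060 and 6 vs 0 gives p = 0.029, so 6 are needed.
- Uncorrected chi-square: 3 vs 0 gives z = (3/118)/√(0.0127·0.9873·2/118) = 1.74. 4 vs 0 gives z = (4/118)/√(0.0169·0.9831·2/118) = 2.02. So 4 are needed.

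**3. Power for 1% vs 0%.** The 1% is the Discussion's liver injury figure for a component herb. The article gives no placebo rate, so 0% is assumed. With X binomial (118, 0.01):

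- Fisher: P(X ≥ 6) = 0.0013, so 99.9% of such trials miss the excess.
- Chi-square: P(X ≥ 4) = 0.0313, so 96.9% miss it.
- With 106 per group, power is 0.0007 and 0.0222.

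**4. Other scenarios, 118 per group, exact power.** All placebo rates are assumptions.

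| HH333 vs placebo | Fisher | Chi-square |
|---|---|---|
| 2% vs 0% | 3.2% | 21.2% |
| 2% vs 1% | 1.1% | 7.1% |
| 4% vs 2% | 6.0% | 12.7% |
| 5% vs 0% | 54.2% | 84.7% |
| 20% vs 10% | 50.8% | 58.4% |
| 60% vs 50% | 29.8% | 34.3% |

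The last row stands for the proportion with any adverse event, if such events are common in both arms.

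**5. What intervals would say.**

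- The chance of no case at all among 118 patients at a true 1% is 0.99^118 = 0.305.
- With 0/118 on HH333, the within-arm exact upper limit is 1 − 0.025^(1/118) = 3.1%, so the planned interval would not exclude a 1% rate either.
- For the difference with 0/118 in both arms, the Wilson upper limit in each arm is 1.96²/(118 + 1.96²) = 3.15%. The Newcombe interval is then −3.15 to +3.15 points.
- With 0 on HH333 and 3 on placebo, the Newcombe upper limit is +1.0 point, so the limit depends on the counts observed.

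**The case against.** The strongest reply is that the article never makes the error. A reader might infer that it treats p > 0.05 as evidence of safety. No passage says so: the sentence about establishing safety is conditional, stands in the Discussion and does not refer to the test. That stands, and the point here does not depend on it. The article names no other between-group inference that could carry such a conclusion.

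A reader might also infer that the test is the whole safety analysis. It is not. Within-arm intervals, counts, severity grades and causality ratings are planned, and frequency, severity and relationship are compared between arms. A cluster of liver or bleeding events could be seen without a significant p-value. That stands too, but none of these items quantifies the excess over placebo with its uncertainty.

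Thirdly, the 1% belongs to a component herb. The Discussion reports no liver or kidney injury with HH333 in 656 patients, which alone would give an exact upper limit of 1 − 0.025^(1/656) = 0.56%. But the Introduction calls these data retrospective and single-arm, and warns that medical records can be inaccurate. The 1% serves here as an illustration from the article, not as a predicted rate for HH333.

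Finally, low power for rare harms is usual, the title calls the trial a pilot, and about 780 per group would be needed for 80% power at 1% vs 0% (uncorrected formula). This excuses the sample size. It does not support a claim of established safety. Table layouts may sit in an analysis plan that is not shown.

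**Conclusion.** The point holds as a mismatch between the stated method and the conclusion the article looks forward to. At 118 per group, a non-significant adverse event test cannot support the hypothesis that HH333 is safe: an excess of 1% vs 0% would be missed 97% to 99.9% of the time, depending on the test. The assumptions are 0% on placebo, all 118 per group in the safety set, and the test applied to liver injury by itself.

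Two stronger readings should be avoided. The trial is not blind to harm in general: power is 54% to 85% for 5% vs 0%, and 51% to 58% for 20% vs 10%. No miss rate can be attached to bleeding, because the article gives no rate for it; and its 2% for HH333 is an overall adverse event rate, not an excess over placebo. Nor is 3 points a floor on what can be excluded; it is the result for no events in either arm.

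This is a cheap improvement, not a flaw that invalidates the trial.

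**What to change.** In the Safety Analysis section, add the between-group risk difference with a two-sided 95% CI (for example Newcombe or Miettinen-Nurminen) for any adverse event and, separately, for key events already collected: ALT/AST elevation, haemorrhage and serious adverse events. State that p-values from the chi-square or Fisher test are descriptive and that a non-significant result will not be read as evidence of safety.

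In the Discussion, replace the wording about establishing safety with a statement limited to the excess risk that the observed upper confidence limit excludes. If both arms had 0/118 events of a given kind, that would be an excess above about 3.2 points; the actual limit will follow from the counts.

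The cost is a few sentences and some extra table columns, with no new patients or data. The real price is a less favourable safety claim. The Results section reports 12 participants randomised by November 13, 2024 and no data analysis, so on that account the change can still be prespecified.
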